### Outcome measures and data collection

#### Outcome measures

The primary outcome measure will be participants' uptake of HMR; and secondary outcome measure will be participant self-reported medication adherence. HMR uptake will be assessed at three and six months from baseline, and medication adherence at six months.

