#### Baseline data collection

The baseline characteristics of participants will be collected using a self-completed questionnaire. At baseline, the questionnaire will be sent to participants with the plain language statement and consent form. Information collected by the baseline questionnaire includes:

• demographics;

• medication use data, including medication management and problems experienced with medications;

• medication adherence [11];

• health-related quality of life [12]; and

• medication-related risk factors and eligibility for HMR (see Additional file 1: Pharmacy Guild of Australia's HMR consumer brochure).

Participants' medication adherence will be assessed using the self-reported Morisky scale [11]. The Morisky scale comprises four validated items, with responses to each item scored 0 for 'yes' and 1 for 'no' (except for the item 'Are you always careful in taking your medicines?' where the score is reversed). The total score on the Morisky scale ranges between 0 and 4; a score of less than 4 represents nonadherence.

Participants' health-related quality of life will be assessed using the self-reported Short Form (SF)-12^® ^Health Survey [12]. The SF-12^® ^Health Survey consists of 12 validated items relating to physical and mental health function. Responses to the items will be scored and computed using an online scoring program [13]. The scoring method will give two sets of results - Physical Component Summary (PCS) and Mental Component Summary (MCS) scores, with the scores ranging from 0 to 100, zero representing the lowest level of health and 100 representing the highest level of health [14].

Participants in both groups will be assessed for their medication-related risk factors and eligibility for receiving a HMR using the criteria or items in the Pharmacy Guild of Australia's HMR consumer brochure (see Additional file 1). Participants who fulfil one or more of these criteria will be considered eligible for a HMR.

Participants will be contacted by telephone to obtain incomplete or missing responses.

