### Data analysis

All data will be analysed according to intention-to-treat principles. The baseline characteristics of participants in the PIG and UCG will be compared using Chi-square, Mann-Whitney U or Student t-test. Uptake of HMR in the two study groups at three and six months will be compared using Chi-square test. Paired samples t-test or Wilcoxon Signed-Rank test will be used to compare changes in Morisky scores and SF-12^® ^Health Survey scores between the two groups at six months.

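### The Morisky and SF-12 analysis compares unadjusted change scores although baseline scores are collected, which costs precision whenever the baseline to six-month correlation is below 1

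*Protocol article*

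**What the plan says.** The Data analysis section of the protocol article states: "Paired samples t-test or Wilcoxon Signed-Rank test will be used to compare changes in Morisky scores and SF-12", and the sentence ends with "Health Survey scores between the two groups at six months". The operative words are "to compare changes in Morisky scores and SF-12": the compared quantity is therefore the change from baseline, and the contrast is between arms.

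The same section does use baseline data in one other way: "The baseline characteristics of participants in the PIG and UCG will be compared using Chi-square, Mann-Whitney U or Student t-test". That is a check of comparability. No baseline value enters the analysis of any outcome.

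Baseline values exist for both instruments. Under Baseline data collection, "Participants' medication adherence will be assessed using the self-reported Morisky scale", and SF-12 physical (PCS) and mental (MCS) component scores are taken in the same questionnaire, with telephone contact to complete missing responses. Both instruments are repeated at six months. On the scale itself: "The total score on the Morisky scale ranges between 0 and 4; a score of less than 4 represents nonadherence".

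The Outcome measures section says the "secondary outcome measure will be participant self-reported medication adherence". SF-12 appears in data collection and in the analysis, but neither in that section nor in the secondary aim stated in the Background.

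**The concern.** A change score uses the baseline by subtracting it whole, which amounts to fixing its regression coefficient at 1. For the Morisky scale that value is implausible. A resident who starts at 4 can only stay or fall, and one who starts at 0 can only stay or rise, so the slope of the six-month score on baseline should be below 1. Where it is, the change score carries avoidable noise.

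What is at stake is the power and interval width for adherence, the trial's secondary outcome. The sample size was set on HMR uptake alone, so nothing in the plan protects precision for adherence. Replacing the paired test with a valid two-sample test would not settle this, because the unadjusted change would still be the quantity compared.

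**Working it through.** **The plan's own figure.** The Sample size section gives 55 per arm for 3% versus 20% HMR uptake, two-sided alpha 0.05, 80% power. With pooled variance and no continuity correction:

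n = [1.960 × √(2 × 0.115 × 0.885) + 0.842 × √(0.03 × 0.97 + 0.20 × 0.80)]² / 0.17² ≈ 54.1, rounded up to 55.

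The recruitment target reproduces as 55 × 1.40 = 77. Both figures stand. They concern a different outcome, and the article states no SD, effect or power for Morisky or SF-12.

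**Variance of the two comparisons.** Assume equal SDs at baseline and six months, and correlation rho between them. In units of SD²:

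- change score: 2(1 − rho)
- six-month score with linear adjustment for baseline: 1 − rho²
- ratio: 2(1 − rho) / [(1 − rho)(1 + rho)] = 2/(1 + rho), which exceeds 1 for every rho below 1.

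The article gives no rho, so a range is shown. The detectable difference is 2.802 × √(2 × variance / 55), where 2.802 = 1.960 + 0.842, at 55 per arm with no clustering. The last column is the power of the adjusted analysis for an effect that the change score would detect with 80% power: Φ(2.802 × √ratio − 1.960).

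| rho (assumed) | Var, change | Var, adjusted | Ratio | Detectable, change (SD) | Detectable, adjusted (SD) | Power, adjusted |
|---|---|---|---|---|---|---|
| 0.3 | 1.40 | 0.91 | 1.54 | 0.63 | 0.51 | 93.5% |
| 0.5 | 1.00 | 0.75 | 1.33 | 0.53 | 0.46 | 90% |
| 0.7 | 0.60 | 0.51 | 1.18 | 0.41 | 0.38 | 86% |
| 0.9 | 0.20 | 0.19 | 1.05 | 0.24 | 0.23 | 82% |

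With the recruited number less 20% loss (77 × 0.8 = 61.6 per arm) and rho = 0.5, the detectable difference is 2.802 × √(2 × 1.00 / 61.6) = 0.505 SD for change and 2.802 × √(2 × 0.75 / 61.6) = 0.437 SD after adjustment.

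Below rho = 0.5 the change score is less precise even than the six-month score alone, whose variance is 1 on this scale (1.40 against 1 at rho = 0.3).

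**The tests named.** The table treats the plan as if it used a valid two-sample test of changes. It does not: a paired t-test or signed-rank test compares two measurements on the same people and cannot contrast two independent groups. If it were run within each arm and the two results compared, a drift shared by both arms would mislead. A simulation with 55 per arm, 4,000 runs, rho 0.5 or 0.7, a common drift of 0.2 to 0.3 SD and no treatment effect gave a significant intervention arm with a non-significant control arm in 16% to 25% of trials. A two-sample test on the changes was significant in about 5%.

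**The case against.** **Efficiency only.** A properly run two-sample comparison of change scores is a legitimate analysis, and the loss depends wholly on an unstated correlation. At rho = 0.9 it is 5% of variance. This stands as a limit on size. The loss is still above zero for every rho below 1, and avoiding it needs no extra data.

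**Left to the analysis plan.** Covariate detail is commonly deferred to a document not shown here. That would answer a complaint that the article is silent. The article is not silent: it names the change as the compared quantity, and names tests that do not fit the contrast.

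**The figures are for linear adjustment.** They assume normal theory, equal SDs and no clustering. For a five-level score with a ceiling they are approximate, and no gain has been computed for ordinal or logistic regression. This stands, and it argues against splitting Morisky into adherent versus not, which discards information and could offset the gain.

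**A stronger reading that a reader might infer** is that change scores carry baseline differences between the two regions into the effect, and that adjustment would remove this bias. The document does not support it. A change score subtracts the baseline difference. What may remain depends on how the regions behave. As an illustration, take a 0.3-point Morisky gap at baseline, a within-region coefficient of 0.5 and no treatment effect:

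- If both regions regress to a common mean, the change score shows (0.5 − 1) × 0.3 = −0.15 points for the higher-starting arm, so it favours the lower-starting arm. The adjusted analysis shows 0.
- If the gap is stable, the change score shows 0, and the adjusted analysis shows 0.3 − 0.5 × 0.3 = 0.15 points in favour of the higher-starting arm.

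Nothing in the article says which holds. Under Cluster randomisation, one region goes to each arm, so region and arm are confounded under either method.

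**Conclusion.** The point holds as one about precision. The plan discards usable information from a baseline score that it collects, and the change score has 1.05 to 1.54 times the variance of the adjusted comparison for rho from 0.9 to 0.3. At rho = 0.5, 80% power becomes about 90%. This rests on an assumed correlation, equal SDs, linear adjustment and no clustering, and it is approximate for Morisky.

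The consequence falls on adherence, the secondary outcome. SF-12 shares the analysis but not the stated aim, and the primary outcome and its sample size are untouched. The change is worth making because the same sentence has to be rewritten anyway to remove tests that cannot compare independent groups. It should not be presented as a cure for differences between the regions.

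**What to change.** Replace the last sentence of the Data analysis section with wording to this effect: six-month scores will be compared between arms in a regression model that includes arm and the participant's own baseline score and accounts for village. The model will be linear for PCS and MCS, and ordinal or linear on the full 0 to 4 score for Morisky. The adjusted between-arm estimate will be reported with its confidence interval, and change scores will be given as description only.

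Do not dichotomise Morisky for this comparison. With only ten villages, the method of accounting for village should be one suited to few clusters. State alongside it that one region is allocated to each arm, so that neither the baseline term nor the village term separates a regional difference from the intervention effect.

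The cost is a few lines of analysis wording and no new data. Participants without a baseline score would need the telephone completion already planned, or a simple imputation of the baseline value.

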### Ethics

This study has been approved by the Monash University Human Research Ethics Committee. Written informed consent will be obtained from all RLOs and participants at the time of enrolment.

### Study timeline

Ethics approval: December 2010

Trial commencement: January 2011 (recruitment of RLOs and retirement villages)

Recruitment of participants and baseline data collection: February - March 2011

Implementation of interventions: April - June 2011

Three-month follow up: September 2011

Six-month follow up: December 2011

Data analysis: January - February 2012

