### Interventions in the Pharmacist Intervention Group (PIG)

At baseline, participants in the PIG will receive the intervention. The intervention to be tested includes several components:

a. HMR education session

• A pharmacist, who is accredited to undertake HMRs, will visit the PIG participants at their villages to deliver a group education session about the role of and benefits from HMR. Information leaflets about HMR will be given out to participants during these education sessions.

b. Medication risk assessment

• A medication risk assessment checklist will be adapted from a screening tool that was previously developed and published by the Pharmacy Guild of Australia (see Additional file 1: Pharmacy Guild of Australia's HMR consumer brochure). The HMR consumer brochure includes a self-administered checklist (with tick boxes) consisting of 16 items assessing a person's risk factors for medication-related problems (e.g. having recent hospitalisation, using multiple medicines, having recent changes to medication regimen, and using low therapeutic index medicines). The checklist will be completed by participants after the education session, with the pharmacist taking them through each question. The completed checklist will be used by the pharmacist to identify participants who have medication risk factors and thus could potentially benefit from a HMR.

c. New referral process for HMR

• Participants identified as having one or more medication risk factors will be referred to their GP. Referral will be made by asking the at-risk participant to give the completed medication risk checklist to their GP during their next GP visit and discuss the need for a HMR.

The group education session, including completion of the medication risk checklist, will take approximately one and a half hours.

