### Three-month follow up

At three months from baseline, participants in both the PIG and the UCG will be interviewed by telephone to assess their HMR uptake. In addition, participants in the PIG will also be assessed for their experience of the pharmacist-education session about the HMR service. Participants' uptake of HMR will be measured as the proportion of participants who have had at least one HMR since baseline.

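### Baseline denotes two events that the timeline separates, so the three- and six-month window for the primary outcome is undefined and does not match the calendar

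*Protocol article*

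**What the plan says.** Two sections of the protocol article attach the word baseline to different events.

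- Interventions in the Pharmacist Intervention Group: "At baseline, participants in the PIG will receive the intervention".
- Baseline data collection: "At baseline, the questionnaire will be sent to participants with the plain language statement and consent form". This applies to both arms.

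The Study timeline puts these events in separate periods: "Recruitment of participants and baseline data collection: February - March 2011", then "Implementation of interventions: April - June 2011".

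The primary outcome depends on the same word. Under Three-month follow up, uptake is "the proportion of participants who have had at least one HMR since baseline". Under Six-month follow up, the groups are compared six months from baseline. The timeline gives each contact a single month for all participants: "Three-month follow up: September 2011" and "Six-month follow up: December 2011".

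The UCG receives no session. The section on its routine care describes six months of observation but does not say when they start.

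**The concern.** Cumulative uptake depends directly on how long residents are observed. If day 0 is ambiguous, so is the primary outcome: one analyst could count HMRs from the questionnaire and another from the session, and both would follow the text. The September and December contacts then yield windows longer than the labels say, except for villages whose sessions fall in June.

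Two things are at stake. The control rate behind the sample size (3% at six months) belongs to a six-month window and not to a longer one. And a window opened at the questionnaire includes time before the PIG has been treated, when both arms are under usual care, which dilutes the contrast.

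**Working it through.** **Inputs.** From Sample size: UCG uptake of 1.5%, 3% and 6% at 3, 6 and 12 months, which is linear at 0.5 points per month; PIG uptake of 20% at six months; 80% power; two-sided alpha 0.05; 55 per group, 77 after inflation. From Study timeline: questionnaire February-March, intervention April-June, contacts in September and December 2011.

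**1. The plan's own figure.** With pooled variance under the null and no continuity correction,

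n = [1.960·√(2p̄(1−p̄)) + 0.842·√(p₁(1−p₁) + p₂(1−p₂))]² / (p₂−p₁)²

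For p₁ = 0.03, p₂ = 0.20, p̄ = 0.115: (0.884 + 0.366)² / 0.0289 = 54.1, rounded up to 55. Then 55 × 1.40 = 77. Both stated figures reproduce. Power at exactly 55 per arm is 81%.

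**2. Windows implied by the calendar** (difference in calendar months)

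| Baseline taken as | To September (three-month label) | To December (six-month label) |
|---|---|---|
| Questionnaire, Feb-Mar | 6-7 | 9-10 |
| Session, Apr-Jun | 3-5 | 6-8 |

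Using extreme dates within the months, the questionnaire row becomes 5.1-7.9 and 8.0-10.9, and the session row 2.1-6.0 and 5.1-9.0. By calendar month, June sessions are on time, May sessions one month late and April sessions two months late.

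**3. Gap between the two baselines.** March to April is 1 month and February to June is 4 months, so a questionnaire baseline puts 1-4 untreated months into the PIG window.

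**4. If each arm used its own baseline event.** UCG 9-10 months, PIG 6-8 months: the UCG window is longer by 9 − 8 = 1 to 10 − 6 = 4 months. At 0.5 points per month that adds 0.5-2 points to UCG uptake, which narrows the difference and so works against the intervention.

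**5. Expected UCG uptake over the longer window.** 0.5 × 9 = 4.5% and 0.5 × 10 = 5.0%, against the planned 3%. From a session-based clock, 6-8 months gives 3.0-4.0%.

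**6. Power at 55 per arm** (same formula solved for power, clustering ignored). The article gives no PIG uptake beyond six months, so three assumptions are shown:

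| Assumption for the PIG | 9 months | 10 months | Power |
|---|---|---|---|
| Held at 20% | 4.5% v 20% | 5% v 20% | 70%, 67% |
| Same extra background in both arms (17 points kept) | 4.5% v 21.5% | 5% v 22% | 76%, 75% |
| Scales with time (20% × 9/6, 20% × 10/6) | 4.5% v 30% | 5% v 33% | 95%, 97% |

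Under the first assumption, 80% power needs 70-76 per group before inflation; under the second, 61-63.

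**The case against.** A reader might infer that the arms are observed over different windows. The article does not say so. The follow-up sections use the same wording for both groups, the timeline gives one month per contact without splitting by arm, and the same questionnaire goes to both groups. A common questionnaire baseline gives equal windows. The 1-4 month difference arises only if the PIG clock starts at the session and the UCG clock at the questionnaire, which no section prescribes. Even then the bias is small beside the planned 17-point difference and runs against the intervention.

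A reader might also infer that follow-up always lands far beyond three and six months. That holds only from the questionnaire. Counted from June, September and December are exactly three and six months, so the calendar may have been built from the end of the intervention period. A month-level timeline in a condensed article need not carry per-village call dates.

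Finally, a reader might quote 67-70% as the power of the trial. That figure lengthens the control window while holding PIG uptake at its six-month value. Other assumptions leave power nearly intact or raise it.

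All three limits stand. They do not remove the contradiction. The article itself fixes both meanings of baseline and the dates that separate them, so this is not detail left to a fuller document. The reading that best fits the calendar, a session baseline, is on time only for June villages and gives the UCG no start date.

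**Conclusion.** The point holds as an inconsistency in how the primary outcome window is defined. Baseline has two meanings, 1-4 months apart, and the fixed contacts match the three- and six-month labels only for PIG villages with June sessions. With a common questionnaire baseline, the windows are equal between arms but overlong (6-7 and 9-10 months), and they include untreated PIG time. Expected UCG uptake at the last contact is then 4.5-5.0% instead of 3%, assuming the plan's linear rate.

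No firm power loss can be stated. At 55 per arm and ignoring clustering, power ranges from about 67% to 97%, depending on an uptake figure that the article does not give. A difference in windows between arms is a possibility left open by the wording and not something the plan specifies. The matter should be corrected, and wording plus a call schedule will do it.

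**What to change.** Define one time zero that applies to both arms. One option is the date of the PIG village's session, with a date set in advance for each UCG village; pairing UCG villages with PIG villages is one way to set that date, not the only one. Keeping the questionnaire as time zero and counting strictly to six months would leave the PIG only 6 − 4 = 2 to 6 − 1 = 5 months after its session.

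Ask for the date of any HMR at each call and when it is verified. The article plans verification where possible but does not say that dates are collected. Count only HMRs dated within three and six months after time zero, and time the calls from it. Reconcile the intervention section, the baseline data section and the Study timeline so that they name the same event. The article already places the offer to the UCG after the study period, so that needs no separate change once time zero is fixed.

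Costs: calls spread over about three months instead of falling in single rounds; HMR dates must be recorded; and residents who have an HMR between consent and time zero stay in the denominator as non-events.

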## Discussion

To our knowledge this will be the first study to develop and test an intervention to improve the uptake of medication review services by retirement village residents in Australia, with a view to decreasing medication risk. Most previous research on medication review uptake has focused on the general populations living in the community or war veterans [15-17]. We will use a multi-faceted interventional approach targeting residents and their health professionals for increasing the uptake of HMR, as suggested by stakeholders. The effectiveness of such interventions (patient education and GP feedback) in increasing the uptake of HMRs has been well-established [16,18]. Our study is endorsed and supported by RRVV and the Council on the Ageing Victoria (COTA). Such collaborations with RRVV and COTA, including the input from RLOs, will facilitate the recruitment and conduct of this study.

## List of abbreviations

HMR(s): Home Medicines Review(s); RLOs: Resident Liaison Officers; RRVV: Residents of Retirement Villages Victoria Inc.; COTA: Council on the Ageing Victoria; GP(s): general practitioner(s); RCT: Randomised Controlled Trial; PIG: Pharmacist Intervention Group; UCG: Usual Care Group; PCS: Physical Component Summary; MCS: Mental Component Summary; SF−12^® ^Health survey: Short Form−12^® ^Health Survey.
